### Data collection

At baseline participants wear the axivity accelerometer for at least seven days before randomisation and complete the baseline questionnaires (either using an online link or paper copy sent by post) before the baseline home visit. At follow-up, the accelerometer is posted to participants in advance of their follow up visit, and the questionnaires are sent to participants once the follow-up visit has been booked (online link or paper as described above). The study visits will be conducted face to face by a member of the research team at participants’ home, a community venue or at their GP practice and completed in line with Government COVID-19 guidance, including NHS infection control procedures. If in person data collection cannot be completed, assessments will take place remotely online or using video conferencing tools. All data collected from participants is stored in a secure password protected database. All participants will receive a £20 high street voucher at completion of follow-up. All data is collected according to a data management plan.

### Collection of SnackApp^TM^ data

The Fitbit Versa 2 collects various measures of physical activity data and displays these data using a bespoke SnackApp^TM^ clockface (see Fig. 3). The SnackApp^TM^ clockface, which is set as default, provides immediate feedback on the number of activity snacks, ‘active minutes’ (i.e. MVPA) and the number of steps users have achieved as measured by Fitbit Versa 2 watch. The clockface on the Fitbit smartwatch downloads the data to a ‘companion app’ via Bluetooth low energy which sit within the Fitbit app environment. With an internet connection, the companion app uploads the data to the Snacktivity™ application programming interface (API) where they are stored in PostgreSQL databases hosted on a secure encrypted Google server. Engagement analytic from the SnackApp^TM^ will be collected and defined as participants’ use and interactions with the SnackApp^TM^ and Fitbit clockface.

**Fig. 3 Fig3:**
[figure not shown]
SnackApp^TM^ clockface

### Adverse event reporting

There is no reason to assume that this trial will lead to an excess of adverse events. The intervention consists of HCPs/researchers promoting short bouts of MVPA within everyday life and use of a commercially available physical activity device to monitor activity, along with a mobile phone app to log movement, none of which are likely to create harm. Furthermore, the promotion of physical activity by health providers is already part of standard care and has been demonstrated as being low risk for all citizens in England as per the NHS Making Every Contact Count Campaign [42] without specific follow-up for adverse events. Therefore, no adverse events will be collected.

### Serious adverse events (SAE)

The research team at site (where applicable) will report all SAEs that are not defined as protocol exempt in an expedited manner. The following are ‘protocol exempt’ SAEs: events related to the participants pre-existing condition(s) (pre-existing conditions are medical conditions that existed before entering the trial, or for which they have already consulted medical advice, as identified on the baseline questionnaire (as per the diseases/conditions specified in Table 3)); and hospital visits for any elective procedures. Musculoskeletal and bone injuries/fractures, and trips and fall injuries are regarded as expected SAEs and are recorded on the follow-up case report forms.

**Table 3 Tab3:** Protocol exempt SAEs relating to pre-existing conditions

Cancer	Sarcopenia (loss of muscle strength)
Type 1 diabetes	Chronic obstructive pulmonary disease
Type 2 diabetes	Asthma
High cholesterol	Kidney disease
High blood pressure	Back pain resulting in time off work
Heart disease, heart attack, angina, aneurysm	Rheumatoid arthritis
Stroke	Osteoarthritis
Depression or anxiety	Neurological condition (e.g. epilepsy, myalgic encephalomyelitis, or multiple sclerosis
Dementia or Alzheimer’s disease	COVID-19
Osteoporosis	Foot/ankle problem affecting patient’s mobility
Obesity	

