### Participant eligibility

#### Inclusion

Inactive, moderately inactive or moderately active (as measured by the GPPAQ) (27).Able to provide informed written consent.Aged ≥ 18 years.Own a mobile phone capable of hosting apps (Apple and Android).Agreement for their HCP to be notified of their involvement in the study (if applicable).

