#### Exclusion criteria

Unable to understand English sufficiently to complete the trial assessments.Women known to be pregnant or breast feeding.

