### Trial oversight and management

The Trial Management Group, which includes two members of the patient advisory group, will meet regularly (approximately every month) to ensure successful implementation and delivery of the trial. They will monitor participant recruitment; any departure from the expected recruitment rate will be dealt with according to the specific issues that arise. A joint independent Trial Steering Committee and Data Monitoring Committee (TSC/DMC) has been created for the Snacktivity™ feasibility trial. The TSC/DMC will meet at least twice a year or as required depending on the needs of the trial. The joint TSC/DMC will provide overall oversight of the trial, including the practical aspects of the trial, as well as ensuring that the trial is run in a way which is both safe for the participants and provides appropriate feasibility data to the sponsor and investigators.

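### The SAE exemption for pre-existing conditions has no exception for events that may also be related to the promoted activity or a trial assessment, and it overlaps with the expected-SAE class

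*Protocol article*

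**What the plan says.** All of this is in the protocol article.

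- **Inclusion and Exclusion criteria.** Entry requires an activity class ("Inactive, moderately inactive or moderately active (as measured by the GPPAQ"), age, a suitable phone, agreement to notify the HCP where applicable, and consent ("Able to provide informed written consent"). The full exclusion list is: "Unable to understand English sufficiently to complete the trial assessments.Women known to be pregnant or breast feeding". No disease is an exclusion.
- **Adverse event reporting.** After arguing that the intervention is low risk, the section ends: "Therefore, no adverse events will be collected".
- **Serious adverse events (SAE).** Sites "will report all SAEs that are not defined as protocol exempt in an expedited manner". There are two exempt classes: "events related to the participants pre-existing condition(s", as identified on the baseline questionnaire and listed in Table 3, and hospital visits for elective procedures. A further sentence treats musculoskeletal and bone injuries, fractures, trips and falls as expected SAEs, recorded on the follow-up case report forms.
- **Trial oversight and management.** The joint TSC/DMC's role includes "ensuring that the trial is run in a way which is both safe for the participants".

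**The concern.** The exemption asks one question: is the event related to a condition that the participant already had? The question that matters for the safety of an activity intervention is a different one: could the event also be related to the activity, the advice or a trial procedure? The two causes can coexist. Exertion may provoke an event in someone whose disease makes it possible, and a rule that looks only at the disease removes that event from expedited reporting.

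At stake is what the TSC/DMC can see, and what is carried forward. The low-risk statement in the Adverse event reporting section is a premise of the trial. Under Table 1, if all four criteria are green, the full trial proceeds with the protocol unchanged unless the interviews or the team's experience point to an improvement. The exemption would then pass into a large trial without the premise having been checked in the participants for whom it is least certain.

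**Working it through.** No sample size, power or rate enters this point, so the check is a comparison of sections.

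**Step 1: who can enter.** Table 3 has 11 entries in the left column and 10 in the right, 11 + 10 = 21 in all. They include heart disease, heart attack, angina and aneurysm (one entry), stroke, high blood pressure, chronic obstructive pulmonary disease, asthma, osteoporosis and sarcopenia. None appears among the exclusions. The one entry criterion that could restrict a Table 3 condition is capacity to consent, which bears mainly on dementia. The Recruitment section identifies patients from general practice and NHS Trust records of booked consultations, so people with these conditions are a natural part of the recruited population.

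**Step 2: apply the exemption.** Take a participant with heart disease recorded at baseline who has a cardiac SAE during an activity snack.

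- Is it related to a pre-existing Table 3 condition? Yes, so it is exempt.
- Does the text withdraw the exemption because the event may also be related to the activity? No such condition is stated.
- Result: not reported in an expedited manner.

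The same holds for an event during a trial assessment, for example the squat-position dynamometer test, if it relates to a listed condition.

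**Step 3: look for another safety route.**

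| Route in the article | Does it capture the Step 2 event? |
|---|---|
| Non-serious adverse events | Not collected |
| Expected SAEs on the follow-up form | Covers musculoskeletal and bone injuries, fractures, trips and falls; a cardiac event is not among them |
| Diseases/conditions and healthcare utilisation at follow-up (Table 2) | Might reveal it indirectly; the resource-use items are presented as a pilot for the cost-effectiveness study, and neither item is described as safety data |

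No described safety route brings the event to the TSC/DMC.

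**Step 4: check the classes against each other.** Osteoporosis, osteoarthritis, back pain with time off work and foot/ankle problems are all in Table 3. A serious fracture in a participant with osteoporosis can be judged related to that condition, which makes it exempt. It is also a fracture, which makes it an expected SAE to be recorded on the follow-up form. The same fracture in a participant with no Table 3 condition is not exempt, so on the section's first sentence it is reported in an expedited manner as well as recorded. The section does not say which rule governs when both apply.

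**The case against.** The strongest reply is that the article condenses a full protocol (version 7.0) that is not shown, and that causality assessment, the content of the SAE form and tables for the committee are commonly left to that document. This stands in part: it cannot be said that no causality assessment exists, and the absence of a form field or a table is not a finding. It does not remove the point, because the article itself states the exemption, with its list, and gives relatedness to the intervention no role in it.

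A second reply is that the intervention is gentle: snacks last 2 to 5 min, participants work towards the goal, and the comparator is also advised towards 150 min of MVPA per week. That supports a low expected event rate. It is not a reason to exempt events that may be related.

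Several stronger readings are tempting, but the text does not support them:

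- *Exempt events are concealed or never recorded.* The exemption is from expedited reporting. The section does not say that exempt SAEs go unrecorded or are withheld from the committee.
- *Falls and fractures are lost in participants without follow-up.* The section does not say that the follow-up form is the sole route, and expected SAEs are not listed as an exempt class.
- *Any heart attack in a participant with high blood pressure is exempt.* High blood pressure and heart disease are separate entries, and a site would have to judge relation. The example is clear only for known heart disease.
- *The TSC/DMC cannot do its safety work.* Non-exempt SAEs, including those in participants with Table 3 conditions, are still reported.

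**Conclusion.** The point holds as a badly fixed reporting rule. An SAE related to a Table 3 condition is exempt from expedited reporting even where the promoted activity, the advice or a trial assessment may have contributed, and the article describes no other safety route for it. The exempt and expected classes also overlap without a rule of precedence.

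Its size cannot be given as a number of events. The documents state neither the prevalence of Table 3 conditions nor an SAE rate for 80 participants over 12 weeks. A reader might infer a large effect from the 21 listed conditions, but counting people with a condition does not estimate harm. Few SAEs may be affected in this trial; the larger consequence is for a phase III trial that inherits the rule.

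The conclusion assumes that the exemption in the full protocol reads as it does in the article. If version 7.0 already withdraws the exemption for possibly related events, that part is met by stating so. Safety is not among the progression criteria, so the feasibility outcomes are unaffected. This is a worthwhile correction and does not call the trial's conduct into question.

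**What to change.** In the Serious adverse events section:

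1. Add one sentence: an SAE related to a pre-existing Table 3 condition is exempt only if it is also assessed as unrelated to the intervention, the usual-care activity advice and the trial assessments. Any other such SAE is reported in an expedited manner.
2. Reconcile the exempt and expected classes. State which rule governs an event in both, such as a fracture in a participant with osteoporosis, and whether an expected SAE is reported in an expedited manner as well as recorded on the follow-up form.

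The cost is a short amendment, a relatedness judgement on each such SAE if sites do not already make one, and a few more reports. The Trial progress section gives 72 participants with baseline complete and follow-up ongoing, so the amendment would apply to the remaining follow-up and, more importantly, to the phase III protocol. Eligibility and clinical care are unchanged.

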### Statistical considerations and data analysis

The feasibility trial aims to recruit 80 participants over 5 months and the sample size is based on recommended sample sizes for feasibility and pilot trials [43]. This means that we will be able to estimate a Snacktivity™ adherence rate of 65% to within a 95% confidence interval of ± 14.8% (based on *n* = 40); a physical activity adherence rate of 60% to within a 95% confidence interval of ± 15.2% (based on *n* = 40); and an attrition rate of 20% to within a 95% confidence interval of ± 8.8% (based on *n* = 80). Based on a response rate of between 1 and 2%, 4000 to 5000 people will need to be invited to participate in the trial to achieve the required number of participants.

A separate statistical analysis plan will provide a more comprehensive description of the planned statistical analyses. The data analysis for this feasibility trial will be mainly descriptive, and focus on confidence interval estimation, with no hypothesis testing performed and no p-values presented. A brief outline of the planned analyses in relation to the stop–go criteria for this feasibility trial is provided. Recruitment and attrition rates will be analysed by pooling the two randomised groups. Adherence (Snacktivity™ and physical activity) rates will be assessed for the Snacktivity*™* group only. Progression criteria will be summarised as proportions and percentages with 95% confidence intervals. We will collect data on the number of invitations sent, and aggregated data on the age and gender of invitees to compare with the trial participants.

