### Recruitment of participants

Participating general practices and NHS Trusts will search their electronic records to identify patients who are ≥ 18 years and have a health care consultation booked during the recruitment phase of the trial. These individuals will be sent a consultation appointment letter (or reminder of the upcoming appointment), along with the trial invitation letter, participant information sheet (PIS), expression of interest form (EOI) and the General Practice Physical Activity Questionnaire (GPPAQ) for screening physical activity status [27]. Those classed as inactive/moderately inactive/moderately active according to the GPPAQ (based on questions 1, 2a, and 2b) will be contacted by telephone to complete eligibility screening with a member of the research team. If a general practice or NHS Trust service routinely uses, or wishes to use, Short Message Service text messages to send patients details of their scheduled appointments and/or to notify them about this study, a study invite link will be added to these text messages where the trial documents referred to above can be accessed by those interested in taking part.

Clinicians/HCPs can also raise the topic of the Snacktivity™ study in routine consultations and those interested in discussing the trial further will be asked to complete the EOI form and GPPAQ, which will be passed on to the research team and these potential participants will complete eligibility screening with the research team by telephone. Potential participants can also be invited to take part in the study via community settings, including social media. These participants will either be sent the recruitment packs in the post or asked to complete the study documents electronically via the study invitation link as detailed above.

For all routes of recruitment, potentially eligible participants will be contacted by telephone by a member of the research team to complete further and final eligibility screening (see below for the full list of criteria applied). If eligible, a baseline visit will be booked to collect assessment data. For participants recruited via a reminder letter this will take place prior to participants’ health/intervention consultation appointment.

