### Progression criteria for phase III trial and stop–go criteria

The decision of whether to continue to the phase III trial will be guided by the assessment of the data collected during the feasibility trial (both quantitative and qualitative). For the quantitative data (Table 1), the following pre-defined stop–go criteria will be used:*Recruitment*: defined as the number/percentage of people randomised against the recruitment target of 80 participants over 5 months.Snacktivity*™ adherence*: defined as the number of physical activity snacks achieved (defined as minimum of four bouts of MVPA lasting ≥ 2 min on average each day over 12 weeks) assessed by the Fitbit monitoring device (in the Snacktivity*™* arm only).*Physical activity adherence*: defined as the proportion of participants who are accumulating a total weekly average of at least 105 min of MVPA (~ 15 min daily) (in the Snacktivity*™* arm only).*Attrition*: defined as withdrawal from the trial and/or no follow-up data available.

**Table 1 Tab1:** Traffic light criteria

Green	At least 80% of the target sample size is recruited
	At least 65% of the intervention group are achieving Snacktivity™ adherence
	At least 60% of the intervention group are achieving physical activity adherence
	Attrition < 21%
If all four criteria are met, we will proceed to the full trial with the protocol unchanged (unless there is a clear indication from the qualitative interviews and our experience that would improve the protocol)	
Amber	50–79% of the target sample size is recruited
	45–64% of the intervention group are achieving Snacktivity™ adherence
	45–59% of the intervention group are achieving physical activity adherence
	Attrition 21–35%
If one or more of our amber criteria are met, we will plan to adapt the protocol in light of the results of the feedback from the qualitative interviews and our experience to improve which ever criteria are not at the ‘green light’ level before proceeding to the full trial	
Red	< 50% of the target sample size is recruited
	< 45% of the intervention group are achieving Snacktivity™ adherence
	< 45% of the intervention group are achieving physical activity adherence
	Attrition > 35%
If one or more of these criteria are met, we would consider the current protocol not feasible and not progress to the phase III RCT with the current protocol	

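### The stated range of invitations does not follow from the stated response rate: for 80 participants, 1 to 2% needs 4000 to 8000 invitations, not 4000 to 5000

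*Protocol article*

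**What the plan says.** Under Statistical considerations and data analysis, the target is set first: "The feasibility trial aims to recruit 80 participants over 5 months". The same paragraph ends with the invitation plan: "Based on a response rate of between 1 and 2%, 4000 to 5000 people will need to be invited". The sentence gives the purpose of that number as reaching the required number of participants. It attaches no separate rate for the step from reply to randomisation, and makes no deduction for people who join without an invitation.

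Under Progression criteria for phase III trial and stop–go criteria, recruitment is "defined as the number/percentage of people randomised against the recruitment target of 80 participants over 5 months". Table 1 sets green at "At least 80% of the target sample size is recruited" and amber at "50–79% of the target sample size is recruited".

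Recruitment of participants describes routes other than appointment letters and text messages. Clinicians may raise the study in consultations, and "Potential participants can also be invited to take part in the study via community settings, including social media". No number of participants is assigned to any route.

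**The concern.** The rate and the invitation count sit in one sentence and are presented as premise and result. For a fixed target, invitations are inversely proportional to the rate, so a two-fold range of rates must give a two-fold range of invitations. The stated range runs from 4000 to 5000, a factor of only 1.25. One of the two ranges must therefore be wrong or incomplete.

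What is at stake is the recruitment planning figure. Recruitment is one of the four stop–go criteria, and examining the recruitment rate is the first listed aim of the trial. The trial will also count the invitations it sends. A reader who sets that count against the planned one has an expected yield that contradicts itself: 1 to 2% by the stated rate, but 1.6 to 2.0% by the stated invitations.

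**Working it through.** **Inputs, all from the article**
- Target: 80 participants (Statistical considerations and data analysis).
- Response rate: 1% to 2% (same paragraph).
- Stated invitations: 4000 to 5000 (same paragraph).
- Recruitment counted as people randomised; green from 80% of target, amber from 50% to 79% (Progression criteria and Table 1). In participants, green starts at 0.80 × 80 = 64 and amber at 0.50 × 80 = 40.

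**Reproducing the stated figures**, with invitations = target / rate:
- At 2%: 80 / 0.02 = 4000. This matches the lower figure.
- At 1%: 80 / 0.01 = 8000. The stated upper figure is 5000, which is 3000 short.

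**Working backwards** from the stated invitations:
- 80 / 4000 = 2.0%.
- 80 / 5000 = 1.6%.

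So 4000 to 5000 invitations correspond to a yield of 1.6 to 2.0%. That lies inside the stated 1 to 2% but leaves out everything below 1.6%.

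**Other readings tried**

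| Reading | Calculation | Invitations |
|---|---|---|
| Midpoint rate of 1.5% as the upper figure | 80 / 0.015 | 5333 |
| Green threshold as target | 64 / 0.02 to 64 / 0.01 | 3200 to 6400 |
| Target inflated for 20% attrition | 80 / 0.8 = 100, then 100 / 0.02 to 100 / 0.01 | 5000 to 10000 |
| 80% of responders randomised (assumed) | 80 / (0.02 × 0.8) to 80 / (0.01 × 0.8) | 5000 to 10000 |
| 50% of responders randomised (assumed) | 80 / (0.02 × 0.5) to 80 / (0.01 × 0.5) | 8000 to 16000 |

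None gives 4000 to 5000. No single target or constant conversion factor can, because each one that uses the full 1 to 2% keeps the two-fold spread. The lower figure of 4000 comes out only if the rate is read as people randomised per person invited.

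**What the stated invitations would yield at 1%**, with no further invitations and nobody from any other route:
- 5000 × 0.01 = 50 participants; 50 / 80 = 62.5%, amber.
- 4000 × 0.01 = 40 participants; 40 / 80 = 50%, the bottom of amber.
- Invitations needed for green at 1%: 64 / 0.01 = 6400.
- Yield needed for green from 5000 invitations: 64 / 5000 = 1.28%.

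**What does not change.** The half-widths in the same paragraph reproduce from 1.96 × √(p(1 − p)/n):
- 65%, n = 40: 14.8 percentage points.
- 60%, n = 40: 15.2 percentage points.
- 20%, n = 80: 8.8 percentage points.

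None of these uses the response rate.

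**The case against.** The arithmetic is hard to dispute. The case on the other side concerns what follows from it, and most of that case stands.

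**A reader might infer that the trial is set to miss green because of this slip.** The article does not support that. The sentence estimates how many people need to be invited and does not limit the mailing to 5000. Under Trial oversight and management, a group meeting about monthly monitors recruitment and acts on departures from the expected rate, so more invitations could be sent. Consultations, community settings and social media could also add participants, although no numbers are given for them. If the yield really were 1% and the trial fell short, the low yield would be the cause, and the recruitment criterion exists to detect it. Trial progress reports 72 participants recruited with baseline complete, which is 72 / 80 = 90% of target. That does not vindicate the invitation range, because neither the number of invitations sent nor the time taken is given. It does weaken any forecast of a recruitment failure.

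**A reader might also infer that phase III would be under-planned by 3000 / 8000 = 37.5%.** Nothing in the article carries the 5000, or the assumed 1 to 2%, forward. The trial collects the number of invitations sent and examines its own recruitment rate for that purpose, so an observed yield would replace the assumption.

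**A third inference is that 8000 is only a minimum**, because responders must still pass screening and consent. That holds only if the rate means replies. If it means randomised per invited, those losses are already included and 8000 is the answer at 1%. The article does not define the term, and the second meaning is the one that gives 4000.

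What survives is narrow: the two ranges in one sentence disagree, and no appeal to other routes removes this, because the sentence makes no allowance for them.

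**Conclusion.** The invitation range is wrong as written. At the stated 1 to 2%, 80 participants need 4000 to 8000 invitations. The stated maximum of 5000 is sufficient only from a yield of 1.6% upwards and falls 3000 short at 1%. The figure of about 50 participants from 5000 invitations rests on three assumptions: a yield of exactly 1%, no further invitations, and no contribution from other routes.

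This is a minor correction to a recruitment-planning figure. Recruitment is judged on people randomised against 80, not on invitations, so the progression thresholds stand as they are, as do the sample size and the precision statements. The point should not be extended to a predicted amber result or to a shortfall in phase III.

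**What to change.** Change one sentence under Statistical considerations and data analysis, in one of two ways:
- state that 80 participants require 4000 invitations at a rate of 2% and 8000 at 1%; or
- keep 4000 to 5000 and state that this assumes a yield of 1.6 to 2.0%.

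In either case, say that the rate is people randomised per person invited. If the authors did mean replies, they should instead give the assumed share of responders who go on to be randomised and divide by that as well.

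The cost is one sentence. With the first option, the stated invitation workload doubles across its range instead of rising by a quarter. No design feature, threshold or analysis changes.

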### Primary outcome

The primary outcome is the feasibility and acceptability of a subsequent phase III RCT according to pre-specified progression criteria. We are primarily interested in whether the Snacktivity™ intervention and trial are appealing to participants (assessed by the recruitment rate) and if the Snacktivity™ intervention and the evaluation methods are acceptable to participants (measured by Snacktivity™/physical activity adherence and retention rates). We also wish to assess the recruitment and randomisation processes, measure the extent of any intervention contamination, and use data collected in the feasibility trial to review the sample size assumptions for the phase III trial.

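### Recruitment is a count against a fixed target of 80, so the planned 95% CI for a proportion does not apply to it and would be too narrow near target

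*Protocol article*

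**What the plan says.** The section on progression and stop–go criteria defines the recruitment criterion as "the number/percentage of people randomised against the recruitment target of 80 participants over 5 months". Table 1 sets green at "At least 80% of the target sample size is recruited" (64 people) and amber at "50–79% of the target sample size is recruited" (from 40 people).

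Under Statistical considerations and data analysis, the article says "Recruitment and attrition rates will be analysed by pooling the two randomised groups", and shortly afterwards "Progression criteria will be summarised as proportions and percentages with 95% confidence intervals". Neither sentence treats recruitment differently from the other criteria.

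The same section gives expected half-widths for Snacktivity adherence (65% ± 14.8, n = 40), physical activity adherence (60% ± 15.2, n = 40) and attrition (20% ± 8.8, n = 80). It gives none for recruitment and names no interval method. It also says that the number of invitations sent will be collected. The first listed aim of the trial is to examine the recruitment rate to inform phase III.

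**The concern.** For adherence and attrition the denominator is a group of participants, each of whom does or does not have the event, so an interval for a proportion is appropriate. For recruitment the 80 is a number chosen at the planning stage. Nobody within it could fail to be recruited, and the count could in principle pass 80. What varies is how many people come forward from those approached over the recruitment period.

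A binomial interval on randomised/80 treats the shortfall from target as the only source of uncertainty. It therefore narrows as the count approaches 80 and is undefined above 80. The actual uncertainty in a count grows as the count grows.

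What is at stake is the uncertainty attached to the recruitment rate when phase III is planned. An interval that is too tight would make the accrual projection look firmer than one five-month count can support.

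**Working it through.** **Inputs.** Target 80, period 5 months, green limit 0.80 × 80 = 64 and lower amber limit 0.50 × 80 = 40 (criteria section and Table 1). Planned precision figures and 4000 to 5000 invitations at a 1 to 2% response (statistical section). 72 recruited so far (Trial progress).

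**Step 1: reproduce the stated figures.** Normal-approximation (Wald) half-width = 1.96 × √(p(1−p)/n).
- 65%, n = 40: 1.96 × √(0.65 × 0.35/40) = 14.8 points.
- 60%, n = 40: 1.96 × √(0.60 × 0.40/40) = 15.2 points.
- 20%, n = 80: 1.96 × √(0.20 × 0.80/80) = 8.8 points.

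All three match.

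**Step 2: the same formula for recruitment at the green limit.** 1.96 × √(0.80 × 0.20/80) = 8.8 points, so 71.2% to 88.8%. This figure is derived here. The article's own ±8.8 belongs to attrition.

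**Step 3: treat the number randomised as a count.** In normal form the half-width is 1.96 × √x/80. For x = 64 this is 1.96 × 8/80 = 19.6 points. The ratio of binomial to count-based width is √(1−p), so √0.20 = 0.447 at 80% and √0.50 = 0.707 at 50%. Exact Poisson limits are χ²(0.025; 2x)/2 and χ²(0.975; 2x+2)/2. Dividing by 80 gives a percentage of target, and dividing by 5 gives a monthly rate.

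| Randomised | Wald, % of 80 | Clopper–Pearson, % of 80 | Exact Poisson, % of 80 | Exact Poisson, per month | Width ratio, normal forms | Width ratio, exact forms |
|---|---|---|---|---|---|---|
| 40 | 50 ± 11.0 | 38.6 to 61.4 | 35.7 to 68.1 | 5.7 to 10.9 | 0.71 | 0.70 |
| 64 | 80 ± 8.8 | 69.6 to 88.1 | 61.6 to 102.2 | 9.9 to 16.3 | 0.45 | 0.46 |
| 72 | 90 ± 6.6 | 81.2 to 95.6 | 70.4 to 113.3 | 11.3 to 18.1 | 0.32 | 0.33 |
| 80 | 100 ± 0 | 95.5 to 100 | 79.3 to 124.5 | 12.7 to 19.9 | 0 | 0.10 |

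With a Wilson interval at 64/80 the ratio to exact Poisson is 0.43. At the green limit the binomial width is therefore 0.43 to 0.46 of the count-based width, whichever binomial method is used. The row for 72 is illustrative, since the article does not say over what period those participants were recruited.

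**Step 4: does this depend on the Poisson model?** Suppose instead that the 64 arise by binomial sampling from N people invited. The half-width as a percentage of target is then 1.96 × √(64(1 − 64/N))/80. This gives 19.4 points for N = 4000, and 19.5 for both N = 5000 and N = 8000 (80/0.01, the number a 1% response would require for 80). The answer is practically the same.

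**Step 5: what the collected data can give.** The monthly rate at 64 is 64/5 = 12.8. Uptake at 64 would be 1.60% of 4000 invited (Wilson 95% CI 1.26 to 2.04), 1.28% of 5000 (1.00 to 1.63) or 0.80% of 8000 (0.63 to 1.02).

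**The case against.** The best defence is that the article offers only a brief outline, defers to a separate analysis plan that is not shown, names no interval method and states no precision for recruitment. One general sentence covers four criteria and is right for three. The unseen plan may well handle the fourth properly. That limits the weight of the point but does not remove it: the published sentence includes recruitment, and no binomial method makes 80 a sample.

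A second defence is that nothing is decided on the interval. Table 1 compares the observed percentage with fixed limits, and the analysis is descriptive. This stands in full.

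A third is that the Poisson interval has assumptions of its own: a constant arrival rate, a fixed period and an uncapped count. Recruitment here runs through several routes, and the Trial Management Group acts on departures from the expected rate. This is fair, so the assumption must be stated. Extra variation between sites or routes would widen the interval further.

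Four stronger readings are tempting, and the documents do not support them.
- A reader might infer that the summary cannot be turned into a recruitment rate. It can: the count and the five months give a monthly rate, and invitation numbers are collected.
- A reader might infer that social-media recruits have no denominator. The article does not say so. It does not state whether packs sent or link visits are counted for that route.
- A reader might infer that the interval collapses to 100% to 100% when the target is met. That is true only of the Wald form, which the article does not prescribe. Clopper–Pearson gives 95.5% to 100%, still far narrower than 79% to 125%.
- A reader might infer that the criterion says nothing about appeal. The same 64 does fit a two-fold range of uptake, but that concerns the choice of criterion, not the interval. Adherence, retention and interviews also inform the judgement, and the invitation counts allow uptake to be reported beside it.

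**Conclusion.** The point holds as a correction to the reported error bars. As written, the rule places an interval for a proportion on a planning constant. At the green limit that interval is less than half the width supported by the count: about ±8.8 points against 62% to 102% of target. At the 50% limit the understatement is milder, with a ratio of about 0.7, and it grows as recruitment approaches 80.

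The size rests on Poisson arrivals, or nearly equivalently on binomial sampling of invitees, and on a binomial method being what the sentence intends. Progression decisions are unaffected. The consequence is false precision in a quantity reported to plan phase III. It is worth correcting before analysis but is not a fault in the trial's design or its go/no-go rule.

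**What to change.** Amend the sentence so that 95% intervals for proportions apply to the two adherence criteria and attrition, and not to recruitment. For recruitment:

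1. Report the number randomised and its percentage of 80 against the Table 1 limits, without a binomial interval.
2. Report randomised per month over the actual recruitment period with an exact Poisson 95% CI, stating that a constant rate is assumed.
3. Report randomised/invited with a binomial 95% CI, separately by recruitment route, wherever the number invited by that route is known. Where it is not known, give the monthly rate only.

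If the separate analysis plan already does this, the article's sentence only needs to be read, and reported against, in line with it.

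The cost is analysis wording. Invitation numbers are already to be collected and route of recruitment is a minimisation variable, so no new data item is needed for routes with counted invitations. The downside is a visibly wider interval for recruitment.
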